### **3.2. Evaluation criteria**

#### **Principle evaluation criteria:**

Epidemiological read-out – sero-prevalence

To assess the association of centrality with exposure to DENV and CHIKV, we will perform a sero-prevalence study using Rapid Diagnostic kits on children 10-15 years spread across 8-12 schools in Bangkok.

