#### 4.3. Source of recruitment

Children of ages 10-15 years old from 8-12 schools will be invited to participate. The schools will be chosen from a list (below) based on their environmental and centrality typology.

| id_sch     | name                                                                              | type | nb_stu | class         |
|------------|-----------------------------------------------------------------------------------|------|--------|---------------|
| 3110023402 | โรงเรียนรัตนจินนุทิศ                                                              | BMA  | 420    | central-_env- |
| 3110015008 | โรงเรียนสุสันทองประดิษฐ์อนุสรณ์                                                   | BMA  | 152    | central-_env- |
| 10032003   | โรงเรียนสุวรรณพลับพลาพิทยาคม                                                      | OBEC | 671    | central-_env- |
| 3110010609 | โรงเรียนวัดธรรมมาภิรตาราม                                                         | BMA  | 133    | central-_env- |
| 3110012104 | โรงเรียนวัดนวลจันทร์                                                              | BMA  | 205    | central-_env- |
| 3110013706 | โรงเรียนคลองกลั่นต้น                                                              | BMA  | 173    | central-_env- |
| 10032029   | โรงเรียนแจรงฟอนวิทยา                                                              | OBEC | 411    | central-_env- |
| 10032012   | โรงเรียนนพรัตนพาราม                                                               | OBEC | 1200   | central-_env- |
| 3110014705 | โรงเรียนอานวยกนกศิโรตธิน                                                          | BMA  | 200    | central+_env+ |
| 3110013001 | โรงเรียนวัดราชสีห์ธาราม                                                           | BMA  | 110    | central+_env+ |
| 10032013   | โรงเรียนชีโนรสวิทยลัย                                                             | OBEC | 2079   | central+_env+ |
| 10032030   | โรงเรียนวัดบวรมงคล                                                                | OBEC | 400    | central+_env+ |
| 3110022710 | โรงเรียนวัดมะลิ                                                                   | BMA  | 176    | central+_env+ |
| 3110012003 | โรงเรียนเทพวิทยา                                                                  | BMA  | 217    | central+_env+ |
| 3110024503 | โรงเรียนสุเทพาภิวนดอน                                                             | BMA  | 106    | central+_env+ |

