### **5.1. General organisation of the study**

#### **A. Sero-prevalence**

A one-time cross-sectional sero-prevalence study to measure IgG seropositivity will be performed in each of the selected schools in pupils aged 10-15 years old. The total number of participants in the research project is 1000. Collected from 2-3 schools in each of the four area types.

After consent to allow child participation, the pediatrician will use a rapid diagnostic lateral flow blood test to measure the immunity against dengue and chikungunya from the children. The blood sampling will be drawn from the fingertips for two drops (1 drop per test) at the child school. The result will be reported within the same day of the test. Parents will be required to answer the Dengue and Chikungunya questionnaires.

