## 9. STATISTICAL CONSIDERATIONS

Sample size:

Based on the preliminary data showing a difference in prevalence rates according to school centrality and environmental typology (approximately 26% vs 15%), we estimate a necessary sample size of ~210 children for each of the four typologies (Central+/Environmental+, Central+/Environmental-, Central-/Environmental+, Central-/Environmental-).

Sample size was calculated as follows [17]

$$n = (Z_{\alpha/2} + Z_{\beta})^2 \cdot [p_0(1 - p_0) + p_1(1 - p_1)] (p_0 - p_1)^2$$

Where n is the required sample size per treatment arm,  $Z_{\alpha}$  and  $Z_{\beta}$  are constants set by convention according to the accepted  $\alpha$  error and whether a one-sided or two-sided effect,  $p_0$  is the proportion sero-positive in area type 0 (ie Central + or Environment +), and  $p_1$  the proportion areas type 2 (Central – or Environment –).

Assuming a  $p < 0.05$  as acceptable and a study with 90% power, the following constant values are:  $Z_{\alpha/2} = 1.96$  and  $Z_{\beta} = 0.84$ .

Because our preliminary data indicated variation within school centrality and environmental typology, (coefficient of variation ranging from 0.6-1), we used the following formula to estimate the number of different sites for each typology.

$$\text{Site number per typology} = 1 + (Z_{\alpha/2} + Z_{\beta})^2 \cdot [p_0(1 - p_0)/n + p_1(1 - p_1)/n + k^2(p_0^2 + p_1^2)] (p_0 - p_1)^2$$

Where k is the coefficient of variation and n the number of individuals as calculated above. Using  $n=210$  and  $k=0.6$  to 1, we would need at least two and optimally three schools per environmental typology with 80-100 children per school.

Sero-positivity (as defined by the manufacturers instructions) will be analysed by logistic regression with age, sex and centrality (high vs. low) and environmental typology (Open vs Dense) as explanatory variables using R. School mosquito densities will also be included as an explanatory variable. In the subset of individuals collecting mosquitoes in the homes will be taken into account in a separate analysis. Mosquito densities will also be analysed with respect to the environmental typology and meteorological parameters.

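### The figure of 80-100 children per school does not fit the two-school minimum: it gives 160-200 children per typology, against the stated ~210 and a total of 1000

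*Protocol*

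**What the plan says.** Section 9 of the protocol takes a prevalence contrast of "approximately 26% vs 15" per cent from the pilot and concludes: "we estimate a necessary sample size of ~210 children for each of the four typologies". After a second formula for the number of sites it adds: "we would need at least two and optimally three schools per environmental typology with 80-100 children per school".

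The two-school option recurs elsewhere as a permitted design. Section 5.1 A says: "The total number of participants in the research project is 1000. Collected from 2-3 schools in each of the four area types". Section 4.3 says: "Children of ages 10-15 years old from 8-12 schools will be invited to participate". Section 3.2 describes the sample as "spread across 8-12 schools in Bangkok", and the protocol summary also gives 2-3 schools per environment and 8-12 schools. None of these places gives a per-school number other than 80-100.

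**The concern.** A protocol that offers a range of designs should reach its sample size at every point of that range, or say where it does not. Here the lower end (two schools per typology, 8 in all) is presented as sufficient, with one per-school figure for both the minimum and the optimum. Multiplying the protocol's own numbers shows that the minimum falls short of the per-typology requirement even at the top of the per-school range.

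A team could select 8 schools, test 80-100 children in each, comply with section 9, and still finish below both the per-typology size and the overall total. What is at stake is the precision of the per-typology estimates and a clear recruitment target for each school.

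**Working it through.** **Inputs.** All come from section 9 unless noted: p0 = 0.26 and p1 = 0.15; Z for alpha/2 = 1.96; Z for beta = 0.84; about 210 children per typology; 2 or 3 schools per typology; 80-100 children per school. Section 5.1 A gives a total of 1000.

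**Reproducing the stated 210.** I read the formula with the bracket divided by the squared difference:

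n = (1.96 + 0.84)² × [0.26 × 0.74 + 0.15 × 0.85] / (0.26 − 0.15)²
= 7.84 × 0.3199 / 0.0121 = 207.3.

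The pooled-variance version gives 211. The stated figure therefore reproduces, with Z for beta at 0.84.

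**Head-count by design.**

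| Schools per typology | Children per school | Per typology | All four typologies |
|---|---|---|---|
| 2 | 80 | 160 | 640 |
| 2 | 100 | 200 | 800 |
| 3 | 80 | 240 | 960 |
| 3 | 100 | 300 | 1200 |

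The requirement is 210 per typology, or 4 × 210 = 840. The stated total is 1000.

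- Two schools: short by 10 to 50 per typology (10/210 = 5% to 50/210 = 24%). Over 8 schools the shortfall is 40 to 200 against 840, and 200 to 360 against 1000.
- Three schools: 210 is met throughout the range. The total of 1000 needs 1000/12 = 83.3, so about 84 per school.
- Two schools, solved for the per-school number: 210/2 = 105 for the per-typology size, and 1000/8 = 125 for the total.

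**Effect on power.** For two groups of n children, ignoring clustering:

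power = Φ(0.11 / √(0.3199/n) − 1.96)

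- n = 160: 69%
- n = 200: 79%
- n = 210: 80%
- n = 240: 85%
- n = 300: 92%

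The pooled version differs by no more than about one percentage point.

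**Main effects.** Section 9 defines p0 and p1 by the level of centrality or of environment, and its regression enters the two as separate binary variables. Each level then pools two typologies. With 8 schools that is 4 × 80 = 320 to 4 × 100 = 400 children per level, and the same formula gives about 94% to 97%, again ignoring clustering.

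**The case against.** **The total is fixed, so 8 schools could still work.** A reader might infer that an 8-school study cannot reach its size. The documents do not support that. The total of about 1000 is stated without regard to the number of schools. Spread over 8 schools it is 125 each, or 250 per typology, which exceeds 210. The range of 80-100 also fits 1000 children in 10 to 12 schools, so it may have been written with the three-school option in mind. This stands: the defect is that the per-school figure was not adjusted for the two-school minimum.

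**The gap at the upper end is small.** At 100 per school the shortfall is 5% of an approximate target and costs about 2 percentage points of power or less. This also stands. The 80-per-school end is the one that matters for power.

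**The planned test pools typologies.** The regression as described compares levels of centrality and of environment, with 320-400 children per level even at 8 schools. This stands too, so no loss of power below 80% has been shown for those main effects on a head-count basis. But the per-typology size is the requirement the protocol set, and the minimum design does not meet it.

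**Withdrawal of a school, and small schools on the list.** A reader might add that no reserve school is named, or that the smallest listed schools would need very high uptake. Neither is an error in the plan. Section 4.3 offers 34 candidates for 8-12 places, and nothing requires choosing the smallest. Nor must refusals reduce the yield further, since 80-100 can be read as children actually tested.

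**Conclusion.** The point holds as an internal inconsistency. With two schools per typology, 80-100 children per school gives 160-200 per typology and 640-800 in total, against the stated ~210, the implied 840 and the stated 1000. Measured against the per-typology target, the cost is between about 2 and 11 percentage points of power, from about 80% to about 79% or 69%. These figures assume 26% against 15%, a two-sided 5% level and no clustering.

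The finding concerns the pairing of 80-100 with two schools. It does not show that 8 schools are unworkable, nor that the main-effect comparisons fall short on head-count.

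Two other problems in section 9 are separate. The text claims "a study with 90% power" but uses Z for beta of 0.84, the 80% value; 90% would need about 278 per group by the same formula. The site-number formula, with n = 210 and the stated "coefficient of variation ranging from 0.6-1", gives about 23 to 60 sites per typology, again reading the bracket as divided by the squared difference. Correcting either would change the targets used here.

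**What to change.** Make the figures in section 9 agree, and carry the result into the summary and sections 3.2, 4.3 and 5.1. Any one of these would do:

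1. State 3 schools per typology, 12 in total, with about 84 children each (12 × 84 = 1008; 3 × 84 = 252 per typology). This lies within the 8-12 schools already stated and leaves the total at about 1000. The cost is up to four more school visits than the minimum and, because section 5.1 B places traps in every school, up to four more sites monitored weekly for a year.
2. Keep 8 schools as an option, but state at least 105 children per school for 210 per typology, or 125 for 1000 in total, and choose listed schools large enough to supply them. The cost is a narrower choice of schools.
3. Keep 8 schools at 80-100 and restate the size for that option as 160-200 per typology and 640-800 in total, with the power that follows. The cost is an openly lower precision per typology.

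Options 2 and 3 change wording and targets only. None of the three repairs the power constant or the site-number formula. In particular, 252 per typology meets 210 but not the roughly 278 needed for 90% power. It is best to correct those two first and then set the per-school number once.

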| 2. Acronym                          | GeoMosquito                                                                                                                                                                                                                                                                                                                                                                                                                                                                                                                                                                                                                                                                                                 |
| 3. Type of study                    | 
A cross-sectional school-based seroprevalence study among children aged 10-15 years. Sero-conversion to dengue virus and chikungunya virus exposure will be measured by the Dengue IgG Rapid Diagnostic kit and the Chikungunya IgG Rapid Diagnostic kit, respectively.
 
A cross-sectional questionnaire study. Questionnaire about KAP about mosquito-borne diseases among their parents who enrolled in the seroprevalence study
 
A prospective observational study of mosquito sampling study in schools and in the homes of 10% of the recruited children using sticky traps
                                                                                                         |
| 4. Rationale                        | Specific places have the potential for being hotspots of viral transmission because of their conduciveness for mosquitoes and their environmental and demographic characteristics that enable these mosquitoes to find and bite their hosts. These areas are predicted to be responsible for the multiplication of cases at a hyperlocal level. Places that are hyper-connected (by transport networks) contribute significantly to viral spread at a city-wide scale, not least from the above-mentioned hotspots. We hypothesize that hyper-connected intra-urban districts will have a higher exposure to dengue and chikungunya, dependent upon the predicted environmental suitability for mosquitoes. |

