| 5. Principle objective              | Assess the extent of dengue virus and chikungunya virus seropositivity, using Rapid Diagnostic tests for IgG in ~1000 school children, aged 10-15 years of age, spread across 2-3 schools of four different environments classified by their degree of connectivity and extent of built-up area, is associated with highly connected areas and predicted high mosquito abundance areas within Bangkok.                                                                                                                                                                                                                                                                                                      |
| 6. Secondary objectives             | 
Collect mosquito samples in these 8-12 schools
 
Assess knowledge, attitude, and practice about mosquito-borne disease, control measures, and vaccine acceptance among parents
                                                                                                                                                                                                                                                                                                                                                                                                                                                                                                                  |
| 7. Principle criteria of evaluation | Seroprevalence rates                                                                                                                                                                                                                                                                                                                                                                                                                                                                                                                                                                                                                                                                                        |

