As a pilot study, prior to roll-out across Bangkok, dengue virus sero-prevalence rates were measured using the Panbio Indirect IgG ELISA on stored blood samples from 272 children aged 3-15 years from within Bangkok. These were mapped according to their homes and schools, whose environmental typology (satellite imagery for vegetation index, height and surface of buildings) and degree of centrality (services density, frequency of transportation and visits using social media data) were established (see Figures below). The association of the degree of centrality (high vs. low) and the type of environment (Open vs. densely built-up) with sero-prevalence rates was then analysed by logistic regression, taking into account the ages of the individuals.

From this retrospective study, the median (IQR) age of the samples was 10.7 (7.6-12.6) years. DENV sero-prevalence rates among children 3-9 years and 10-15 years were 6.5% and 37.2% respectively. Children going to schools characterized by an open environment or one of low centrality had much lower sero-prevalence rates (Open vs. dense: 16.8% vs. 27.1%; Low vs high centrality: 14.8% vs. 25.2%). There was no difference in sero-prevalence rates according to the degree of centrality of their homes. However, sero-prevalence rates in homes in open environments were higher (27.1% vs. 12.6%) (Fig. 3).

**Figure 3.** Sero-prevalence rates according to landscape category and centrality in children's homes and schools

[figure not shown]

Suwanbamrung et al. [14] conducted a cross-sectional study among children aged 8-13 years from 50 public schools in Kanchanadit district to assess the correlation between knowledge, attitude and practice (KAP) in dengue infection including prevention method compare between children with and without dengue infection experience using 32-items questionnaire. The study shows no significant difference in KAP mean score between the 2 groups, but the children with previous dengue infection had better preventive practice than the other group (OR 1.34, 95%CI 1.03-1.75,  $P=0.032$ ). The study also notes that most children (more than 70%) reported that their source of dengue information came from their teacher. Thus, in addition to the sero-prevalence study, we are also interested in assessing levels of KAP concerning dengue and provide more information about dengue infection and prevention, which can then be applied in their school and household.

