Vongpunsawad et al. [15] conducted sero-prevalence surveys of CHIKV and DENV in Thailand, in which 835 serum samples were obtained from individuals living in central and southern Thailand by using anti-CHIKV and anti-DENV IgG antibodies commercial enzyme-linked immunosorbent assays. Overall seropositivity of CHIKV in children aged < 15 years was 10.3%, of which 17.8% among participants from the south and 2.6% among participants from central Thailand. Seropositivity of DENV was 31.9% among children aged < 9 years in both in the southern and central parts, 55.4% among children aged 10-19 years among southern participants and 62.5% among children aged 10-19 among central participants. The current situation in Bangkok is unknown, but a large scale outbreak occurred all of Thailand in 2018-2019 and *Aedes aegypti* was incriminated as the major vector [16]. We thus anticipate that the sero-prevalence rates will be influenced by the environmental typology as for DENV.

Based on these preliminary findings, this current project aims to expand this sero-prevalence study in a prospective school-based study in children aged 10-15 years old for both DENV and CHIKV infections.

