## 3. **METHODOLOGY**

### **3.1. Type of research**

This study divides into 3 parts

1. A cross-sectional school-based sero-prevalence study among children aged 10-15 years. Sero-conversion to dengue virus and chikungunya exposure will be measured by Dengue IgG Rapid Diagnostic kit and Chikungunya IgM/IgG Rapid Diagnostic kit, respectively (SD Bioline).
2. A cross-sectional questionnaire study. The questionnaire about KAP about mosquito-borne diseases among their parents who enrolled in sero-prevalence study
3. A prospective observational study of mosquito sampling study in schools and in the homes of 10% of the recruited children using sticky traps

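### The CHIKV kit is described two ways with no rule for an IgM-only result, and rapid-test readings are planned and modelled without allowance for test error

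*Protocol*

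**What the plan says.** The primary criterion is seroprevalence. Section 3.2 states: "we will perform a sero-prevalence study using Rapid Diagnostic kits on children 10-15 years spread across 8-12 schools in Bangkok".

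The CHIKV kit is named in two places:
- Summary, item 3: "the Dengue IgG Rapid Diagnostic kit and the Chikungunya IgG Rapid Diagnostic kit, respectively".
- Section 3.1: "Dengue IgG Rapid Diagnostic kit and Chikungunya IgM/IgG Rapid Diagnostic kit, respectively (SD Bioline").

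The marker is IgG throughout. The principal objective (Summary, item 5) is assessed "using Rapid Diagnostic tests for IgG in ~1000 school children", and sections 5 and 5.1.A also name IgG.

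Section 9 leaves the cut-off to the kit maker and models the result directly: "Sero-positivity (as defined by the manufacturers instructions) will be analysed by logistic regression with age, sex and centrality". Its planning rates, about 26% vs 15%, are drawn from the pilot, in which "dengue virus sero-prevalence rates were measured using the Panbio Indirect IgG ELISA on stored blood samples from 272 children".

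For CHIKV, the Background cites an ELISA survey of children under 15 with "17.8% among participants from the south and 2.6% among participants from central Thailand" and 10.3% overall. It then calls the current Bangkok situation unknown after a large outbreak in 2018-2019.

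No blood is kept (6.1), the kits are thrown away once read (6.3), and paper forms are destroyed after double entry (7.2).

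**The concern.** A combined kit can give four readings: neither line, IgG only, IgM only, or both. The study wants IgG as a marker of past infection. If staff follow the manufacturer's definition of a positive and enter one overall result, IgM-only children may be counted. The protocol does not say whether they should be.

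The case report form (section 7.1) carries the test result for each virus but has no instruction to record the lines separately. Once kits and forms are gone, nobody can undo the choice. A statistical analysis plan written later could not recover it either.

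The second issue is test error. Entering the reading as it stands treats the test as error-free, and the sample size carries ELISA-based rates over to a rapid test unchanged. Imperfect Se and Sp bias the reported rates. If error is the same in every area type, they also shrink the contrast between types. Section 5.3 offers the seroprevalence data to health authorities in connection with a dengue vaccine, so the level of the DENV rate matters as well as the contrast.

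**Working it through.** **Step 1. The plan's own sample size.** Inputs from section 9: p0 = 0.26, p1 = 0.15, constants 1.96 and 0.84. The last factor of the printed formula is read as a divisor.

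n = (1.96 + 0.84)² × [0.26 × 0.74 + 0.15 × 0.85] / 0.11² = 7.84 × 0.3199 / 0.0121 = 207.3, which agrees with the stated ~210. The constant 0.84 corresponds to 80% power, not the 90% named beside it. That is a separate matter; 0.84 is kept here.

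**Step 2. DENV under rapid-test error.** The protocol gives no Se or Sp, so both are assumed, and equal in all area types.

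Apparent rate = Se × p + (1 − Sp) × (1 − p), so apparent difference = (Se + Sp − 1) × (p0 − p1).

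| Se/Sp (assumed) | Apparent rates | Difference | n per typology, same formula |
|---|---|---|---|
| 100/100% | 26.0 vs 15.0% | 11.0 points | 207 |
| 90/98% | 24.9 vs 15.2% | 0.88 × 11 = 9.7 points | 264 |
| 80/95% | 24.5 vs 16.3% | 0.75 × 11 = 8.25, about 8.3 points | 370 |

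The rate itself also moves. At the pilot's 37.2% for ages 10-15, the apparent rate is 0.372 × 0.90 + 0.628 × 0.02 = 34.7% at 90/98%, and 0.372 × 0.80 + 0.628 × 0.05 = 32.9% at 80/95%.

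**Step 3. CHIKV at low prevalence.** Take p = 2.6% (the cited central-Thailand figure, treated as true), 1000 children and an assumed Se of 90%. True positives = 1000 × 0.026 × 0.90 = 23.4. False positives = 974 × (1 − Sp).

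| Sp (assumed) | False positives | False share of positives |
|---|---|---|
| 99% | 9.7 | 29.4% |
| 98% | 19.5 | 45.4% |
| 97% | 29.2 | 55.5% |
| 95% | 48.7 | 67.5% |

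Half the positives are false when 1 − Sp = Se × 0.026 / 0.974. The threshold is Sp = 97.3% at Se 100% and 97.9% at Se 80%.

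At the survey's overall 10.3%, with Se 90%, the false share is 8.8% at Sp 99% and 32.6% at Sp 95%.

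**The case against.** Several counter-arguments have force.

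- **A combined kit does no harm by itself.** Its IgG line can be read alone, and the protocol names IgG as the marker in several places. This is true, so the conflict over the kit does not in itself create false positives. What remains is that the protocol never says the IgG line alone decides, and discards everything that would allow a later check.
- **Correction for test error may sit in an analysis plan not shown here.** This is fair, and its absence from section 9 is not an error in itself. But a later plan could use only external Se and Sp, because there is no confirmatory test or validation subset, and it could not recover IgM-only results that were never recorded.
- **Most CHIKV positives are false at the protocol's own prevalence.** A reader might infer this, but the documents do not support it. The 2.6% is a background ELISA figure that section 9 does not use and the Background itself qualifies. The inference also needs a specificity below about 97.3-97.9%, and no specificity is given. Calling the CHIKV results largely noise goes further still.
- **The loss of power is modest for main effects.** Comparing high with low centrality pools two typologies, about 420 vs 420. Ignoring clustering by school, power is still about 90% at Se 90%/Sp 95%. This stands, so bias in the reported rates is the larger issue.
- **The rapid-test rates will be set against ELISA rates.** No section plans such a comparison. The ELISA data serve as background and as sample-size input only.
- **The vaccine use in section 5.3 concerns dengue.** The CHIKV figures therefore have no bearing on it.

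**Conclusion.** The point holds in three parts. First, the Summary and section 3.1 conflict on the CHIKV kit, and no rule covers an IgM-only result. This rests on the text alone. Second, the plan to discard blood, kits and forms makes an unrecorded line irrecoverable, so the matter must be settled before fieldwork. Third, ELISA-based DENV rates were carried to a rapid test without allowance for error.

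The direction of the third part follows from arithmetic if error is equal across area types. Its size rests on assumed accuracy: 11 points become 9.7 at Se/Sp 90/98% and about 8.3 at 80/95%. For CHIKV, if prevalence were as low as 2.6%, about 30% of positives would be false at Sp 99%, and more than half only below about 97.3-97.9%. This is an improvement that should be made; it does not show that the study cannot answer its question.

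**What to change.** 1. Reconcile Summary item 3 with section 3.1 so that one CHIKV kit is named.
2. State in section 9 that a visible IgG line defines CHIKV seropositivity.
3. Have the case report form (section 7.1) record the IgM and IgG lines separately, and report IgM-only results apart from the seroprevalence.
4. State the kits' IgG sensitivity and specificity. Report seroprevalence by typology both raw and corrected for test error, by Rogan-Gladen, (apparent rate + Sp − 1) / (Se + Sp − 1), or a Bayesian equivalent, carrying the uncertainty in Se and Sp.
5. Repeat the logistic model with allowance for misclassification over a stated Se/Sp range, as a sensitivity analysis.

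The cost is one endpoint definition, one extra field on the form and a short analysis addition, with no extra tests or staff. Corrected intervals are wider: by a factor of 1/0.88 = 1.14 at 90/98% and 1/0.75 = 1.33 at 80/95%, before uncertainty in Se and Sp is added. The correction also relies on accuracy values from outside the study.
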